**Primary**							
Exclusive breastfeeding four months (binary)			X				*NCHR*
Exclusive breastfeeding (continuous)	X	X	X				*NCHR*

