**Methods:**

The intervention is tested in a cluster-randomised trial at the municipal level. A comprehensive evaluation approach is taken. The effectiveness of the intervention will be evaluated using survey and register data. Primary outcomes are the proportion of women who breastfeed exclusively at four months postpartum and duration of exclusive breastfeeding measured as a continuous outcome. A process evaluation will be completed to evaluate the implementation of the intervention; a realist evaluation will provide an understanding of the mechanisms of change characterising the intervention. Finally, a health economic evaluation will assess the cost-effectiveness and cost-utility of this complex intervention.

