### Survey data

The primary outcome measure is studied by using self-reported measures collected via self-administered web-based questionnaires. Survey questionnaires are distributed via emails to mothers recruited via the health visiting programme at the following five postpartum time-points: one week, one month, four months, six months and 12 months. Additionally, fathers/partners were invited to a survey at one month postpartum (see Fig. 3 for an overview timeline). From the surveys, we also study a range of secondary outcome measures.

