#### Secondary outcome measures

The secondary objectives are to assess the effectiveness of the breastfeeding support programme on:Duration of exclusive breastfeeding (continuous)Infant readmissions to hospital related to nutritionMothers’ experiences of breastfeeding problemsParental trust in the health visitorMaternal breastfeeding self-efficacyPaternal feeling of inclusion in the breastfeeding supportBreastfeeding in mothers with overweight

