**Secondary**							
Readmission of infant to hospital related to nutrition	X	X					*NPR*
Experienced breastfeeding problems	X	X	X				
Family’s relationship with health visitor	X	X	X			X	
Maternal breastfeeding self-efficacy	X	X	X				
EQ-5 D^*^		X	X				
Partial breastfeeding				X	X		

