### Statistical methods

We use random allocation to remove any influence of both measured and unmeasured variables on treatment allocation. Before conducting regression analyses, descriptive statistics will be applied to assess selection into the trial, baseline equivalence of trial arms and loss to follow-up.

Regression analyses will be applied when analysing primary outcomes. We will account for the clustered nature of data by using random effects models for binary and continuous outcomes [51] and shared frailty models for analysing time-to-event and recurrent events in continuous outcomes [52]. Intention-to-treat analyses will be conducted. These analyses will include all mother-infant dyads in the relevant trial arms irrespective of their compliance or loss to follow-up. Complete-case analyses will be conducted restricted to observations with available outcome measures [53]. For the intention-to-treat analyses, the survey data will be linked to the Danish national registers including all births; and missing outcome data will be handled by inverse probability weighting and missing covariates by multiple imputation from the registers. The probability weights will be estimated by conducting logistic regressions with outcome data (yes vs. no) as dependent variable and the following baseline variables as predictors: maternal educational, maternal age, cohabitation status, partner’s education, household income, occupational status, maternal smoking status, maternal BMI, and maternal as well as paternal psychiatric histories.

The effect of the intensified intervention will be examined by including an interaction term between treatment arms and a binary indicator of the mother being young or having low educational attainment.

All models will be analysed with treatment alone and adjusted for known predictors for breastfeeding duration collected in the survey (smoking status, maternal age, maternal education, parity, mode of delivery, maternal BMI and cohabitation status) and for design variables used in the randomisation (region of Denmark and number of annual births (< 900 births/year vs. ≥ 900 births/year). As the randomisation will hopefully have distributed the characteristics evenly between trial arms, these adjustments are made to increase the robustness of the effect estimations. Missing predictors will be imputed using multiple imputations and the results compared to the complete case analysis.

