#### Health economic assessment

The health economic evaluation will shed light on the total health economic consequences of the intervention, including the intensified intervention. The health economic evaluation will be conducted as a cost-effectiveness analysis measuring health benefits as changes in the proportion of women breastfeeding at four and/or six months postpartum; and as a cost-utility analysis measuring the mothers’ gained quality-adjusted life years (QALYs). We measure QALYs using the widely used EQ-5D survey. QALYs include considerations related to both physical and mental well-being [55].

In both analyses, we assess two types of costs. First, direct costs related to the intervention will be assessed. Here, we distinguish between costs associated with the adaptation of the intervention and costs associated with its operation. Adaptation costs are fixed costs that are unlikely to be incurred by potential future adopters, whereas operating costs are repeated which is why separate reporting of cost types is relevant. Second, we will estimate the indirect costs (or savings) of the intervention. Like for indirect costs, we estimate the impact of the intervention on subjects’ healthcare usage in the primary and secondary healthcare sector. Such usage includes GP services and hospital admissions for both mother and child. We will consider the longest possible follow-up period. Both when considering breastfeeding and QALYs, we report the incremental effectiveness ratio (ICER). The ICER will establish the cost required to increase the share of breastfeeding mothers by a specific percentage and the cost accrued per gained QALY. Summarizing the cost-effectiveness of the intervention using ICERs allows for comparison with other healthcare interventions. Additionally, we will conduct a series of subgroup analyses to evaluate if the cost-effectiveness of the intervention depends on family characteristics.

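### As scheduled, the survey stops measuring exclusive breastfeeding at four months, so survey-based duration is right-censored for about half the mothers

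*Protocol article*

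**What the plan says.** - **Survey waves.** Under Survey data, mothers receive questionnaires at "five postpartum time-points: one week, one month, four months, six months and 12 months".
- **What each wave collects.** Under Data collection, Table 3 is presented as the list of what each wave collects. Its primary row "Exclusive breastfeeding (continuous" is marked at 1 week, 1 month and 4 months, with the National Child Health Register (NCHR) as register source. At 6 and 12 months the only breastfeeding row marked is "Partial breastfeeding", listed as secondary.
- **Status of duration.** The abstract names "duration of exclusive breastfeeding measured as a continuous outcome" as a primary outcome, and overall duration is one of the Objectives. The list of secondary outcome measures also contains "Duration of exclusive breastfeeding (continuous". That difference in status needs reconciling, but is a separate point.
- **Models.** Statistical methods accounts for clustering by "using random effects models for binary and continuous outcomes" and, in the same sentence, by shared frailty models for time-to-event analysis.
- **Register.** Study design says the arms will be compared on breastfeeding duration from national registries. The section that develops this plans a difference-in-difference analysis that includes average weeks of breastfeeding, with data expected in early 2025 at the earliest.

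**The concern.** Duration is a stated objective, the Danish and WHO recommendation is six months, and the Background credits the earlier hospital programme with an effect at six months. The intensified intervention is delivered over the first five months, so its last part falls after the final survey measurement of exclusive breastfeeding. The Background also says that exclusive rates fall sharply around four months, which is where this measurement ends.

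If nothing is added, the survey's randomised comparison of duration describes stopping up to four months only. A benefit that appears mainly after four months would not be seen in it, although a questionnaire is sent at six months anyway. Duration is labelled continuous throughout, and the methods name both a random-effects model and a time-to-event model for continuous outcomes. The text therefore leaves open an analysis that takes four months as the true duration of a censored mother.

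**Working it through.** **Inputs from the protocol article.** From Sample size and power calculations: 49% at four months in the project regions, 56% as target, 8 clusters per arm, ICC 0.001, 111 mothers per cluster, 80% power, 5% significance (taken as two-sided). From Background: at most 14% exclusive at six months, nationally. The 49% is read as exclusive breastfeeding, as that section's odds-ratio sentence implies.

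**1. The plan's own figure.** Two proportions, pooled variance under the null, no continuity correction:

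n = [1.96·√(2·0.525·0.475) + 0.842·√(0.49·0.51 + 0.56·0.44)]² / 0.07² = 798 per arm.

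With design effect 1 + (m − 1)·0.001 and 8m mothers per arm:

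m = 798·0.999 / (8 − 0.798) = 110.7, so 111. Power at 111 is 80.1%.

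The stated 111 reproduces. It concerns the binary four-month outcome only.

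**2. Share of survey durations censored at four months.** This is the proportion still exclusive at that time. With 8 × 111 = 888 mothers per arm:

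- control: 0.49 × 888 = 435
- target: 0.56 × 888 = 497
- average: (0.49 + 0.56)/2 = 52.5%

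The trial has 21 clusters, not 16, so the counts may be larger; the shares do not depend on that.

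**3. Share stopping between four and six months, control arm.** The article gives no regional six-month figure, so this is an assumption with a range:

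| Assumed control proportion at six months | Stop between four and six months |
|---|---|
| 14% (national ceiling) | 0.49 − 0.14 = 35% |
| 12.25% (14% × 49/56, scaled to the regions) | 36.75% |
| 0% (extreme) | 49% |

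At 14%, those who stop are 0.35/0.49 = 71% of control mothers still exclusive at four months.

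**4. Exclusive time outside the survey.** Between four and six months the control mean is (0.49 + 0.14)/2 × 2 = 0.63 months under linear decline. The bounds are 2 × 0.14 = 0.28 and 2 × 0.49 = 0.98. A linear model on durations capped at four months drops this time.

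**5. Illustration of the gain.** Assume proportional hazards lasting to six months, 14% in control at six months, and no further loss after four months.

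- HR = ln 0.56 / ln 0.49 = 0.813
- intervention arm at six months: 0.14^0.813 = 20%
- events to four months: 888 × (0.51 + 0.44) = 844
- events to six months: 888 × (0.86 + 0.80) ≈ 1472 (unrounded proportions)
- power = Φ(|ln HR|·√(events/(4 × 1.11)) − 1.96), where 1.11 is the design effect: about 82% to four months and 97% to six months

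**The case against.** The strongest reply is that duration is not confined to the survey. The same Table 3 row lists the NCHR, Study design announces a between-arm analysis of register duration, and a register analysis of weeks is planned. This stands. A reader might infer that the outcome as a whole cannot show effects after four months; the article does not support that. What remains is narrower. The section on outcome measures says the trial was designed around survey measures and calls the other sources supplementary. Statistical methods handles missing survey outcomes by weighting, not by substituting register values. The article does not say how far the register records exclusive duration.

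Four further points stand:

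- Shared frailty models handle right-censoring, and nothing says duration will be fitted linearly. The model assignment is at most ambiguous.
- A reader might infer that duration capped at four months largely repeats the binary outcome. It does not: 44% to 51% of mothers stop before four months, and the timing of those stops is information that the binary outcome lacks.
- A reader might infer that the cost-effectiveness analysis lacks its six-month data. That section refers to "changes in the proportion of women breastfeeding at four and/or six months postpartum", which does not specify exclusive breastfeeding and makes six months optional; partial breastfeeding is surveyed then.
- The questionnaire wording is not shown. The six-month item might also record when exclusive feeding ended; if so, Table 3 should say so.

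The four-month focus of the binary outcome has a stated rationale in the Danish guidance on solids. That justifies the binary endpoint, but not ending the measurement of duration there.

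**Conclusion.** The point holds for the survey comparison. On the schedule in Table 3, survey-based duration is right-censored at four months for 49% (control) to 56% (target) of mothers, and the survey cannot show effects on exclusive breastfeeding between four and six months. About 35% of control mothers stop in that interval if the national 14% applies to them, and more if the regional figure is lower. Censoring does not invalidate a shared frailty analysis; its hazard ratio then describes stopping up to four months.

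The register may supply later durations, but the only analysis specified for them is a difference-in-difference, expected in 2025 at the earliest. The article does not say that register duration extends survey duration in the randomised comparison. This is a worthwhile, inexpensive improvement and no threat to the binary primary outcome or its sample size. The power gain rests on proportional hazards and full retention to six months, and is an illustration only.

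**What to change.** 1. Add one item to the six-month questionnaire: is the infant still exclusively breastfed and, if not, at what age did that stop? For mothers already past that wave, ask it as recall at twelve months. Data collection began on 26 April 2022 and the article appeared on 8 March 2023, so at publication no mother recruited from that start had reached her twelve-month questionnaire. Mark the item in Table 3.
2. Analyse duration with the shared frailty model already named, censoring at last contact. Do not use a linear random-effects model that takes four months as the true value.
3. If the waves have closed, define survey duration as censored at four months and name the register as the source beyond that.

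Cost: one item in web questionnaires that are already sent, plus wording in the analysis plan. Downsides: recall error, mixed measurement timing for mothers surveyed before the change, and further non-response after four months, given the 30% attrition already expected by then.

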**Secondary**							
Readmission of infant to hospital related to nutrition	X	X					*NPR*
Experienced breastfeeding problems	X	X	X				
Family’s relationship with health visitor	X	X	X			X	
Maternal breastfeeding self-efficacy	X	X	X				
EQ-5 D^*^		X	X				
Partial breastfeeding				X	X		
**Covariates**							
Age	X					X	*SD*
Education	X					X	*SD*
Occupation	X					X	*SD*
Civil status	X					X	*SD*
Smoking	X					X	
BMI^**^	X					X	
Details about the birth (date, mode, infant’s weight)	X						*BR*
Attitude towards breastfeeding	X					X	
Previous breastfeeding experience	X						
Breastfeeding knowledge	X					X	
Sense of support from partner	X						
Assessment of support from health visitor	X					X	

*Abbreviations:*
*BMI* Body Mass Index, *BR* The Birth Register, *NCHR* The National Child Health Register *NPR* The National Patient Register, *PP* postpartum, *SD* Statistics Denmark

^*^European Quality of life – 5 Dimensions (EQ-5D)

^**^Calculated using self-reported weight and height

### Statistical methods

We use random allocation to remove any influence of both measured and unmeasured variables on treatment allocation. Before conducting regression analyses, descriptive statistics will be applied to assess selection into the trial, baseline equivalence of trial arms and loss to follow-up.

Regression analyses will be applied when analysing primary outcomes. We will account for the clustered nature of data by using random effects models for binary and continuous outcomes [51] and shared frailty models for analysing time-to-event and recurrent events in continuous outcomes [52]. Intention-to-treat analyses will be conducted. These analyses will include all mother-infant dyads in the relevant trial arms irrespective of their compliance or loss to follow-up. Complete-case analyses will be conducted restricted to observations with available outcome measures [53]. For the intention-to-treat analyses, the survey data will be linked to the Danish national registers including all births; and missing outcome data will be handled by inverse probability weighting and missing covariates by multiple imputation from the registers. The probability weights will be estimated by conducting logistic regressions with outcome data (yes vs. no) as dependent variable and the following baseline variables as predictors: maternal educational, maternal age, cohabitation status, partner’s education, household income, occupational status, maternal smoking status, maternal BMI, and maternal as well as paternal psychiatric histories.

The effect of the intensified intervention will be examined by including an interaction term between treatment arms and a binary indicator of the mother being young or having low educational attainment.

All models will be analysed with treatment alone and adjusted for known predictors for breastfeeding duration collected in the survey (smoking status, maternal age, maternal education, parity, mode of delivery, maternal BMI and cohabitation status) and for design variables used in the randomisation (region of Denmark and number of annual births (< 900 births/year vs. ≥ 900 births/year). As the randomisation will hopefully have distributed the characteristics evenly between trial arms, these adjustments are made to increase the robustness of the effect estimations. Missing predictors will be imputed using multiple imputations and the results compared to the complete case analysis.

To validate the robustness of the results, the following sensitivity analyses will be performed: First, data will be restricted to mothers having received the full intervention, i.e., including pregnancy visits (June 17 and onwards), to assess the effect of receiving the full intervention compared to mothers having received the intervention without the pregnancy visits (April 26 to June 16); second, observations with no records in registries, most likely an indicator of recent immigration, will be excluded to test whether the effect of the intervention is higher among individuals familiar with the Danish healthcare system than among those who are not familiar with the system; and, third, the worst case scenario assigning no breastfeeding at four months postpartum to all individuals with missing registrations will be used to gauge the minimum effect of the treatment.

The Danish nationwide registries will further allow detailed assessment of selection into the trial (Table 3). Selection into the trial will be examined using register data from 2022, again using inverse probability weighting to assess potential selection effects.

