### Study population

The study setting includes 21 municipalities in Denmark, all of which are situated in the North Denmark Region (*n* = 6) or Region of Southern Denmark (*n* = 15) (see Fig. 1). Denmark consists of a total of five regions. The two selected regions have some of the highest proportions of mothers who are of young age and/or have a low educational attainment. Each of the 21 participating municipalities constitutes a cluster in the trial.

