**Development and implementation**
For the adaptation of the previous successful breastfeeding intervention done by Nilsson and colleagues (2017) in hospital setting, an assessment of the needs of families following discharge from hospital after birth and until six months postpartum was carried out. Programme objectives corresponding to findings from the needs assessment formed the basis of the adaptation. In the adaptation process, a participatory approach including health visitor representatives from each of the intervention municipalities was chosen to enhance ownership, to match the organisational structure of the setting (the Danish Health visiting programme), and to ensure implementation in the intervention municipalities. The final intervention programme consisted of a breastfeeding programme for parents and a related training programme for health visitors. In December 2021, 210 health visitors from the 11 intervention municipalities completed a preparatory 3.5-h e-learning course, and in March 2022 they participated in the 15-h physical attendance interactive training programme supported by a written manual. Following training, the health visitors immediately initiated implementation of the programme in their municipalities

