### Sample size and power calculations

For sample size calculation, an estimated eight clusters in each arm were used, totalling 16 clusters. Expected participation rate was 80% with 30% attrition from the first questionnaire at one week postpartum to the third questionnaire at four months postpartum. A power calculation was made using breastfeeding frequencies from 2016 made available from The National Child Health Register [50]. The ambition was to raise the proportion of women breastfeeding at four months in the intervention clusters to the national level. In the design phase, we obtained data on the mean prevalence of breastfeeding at four months in the project regions (49%) and at national levels (56%) in 2016 from the National Child Health Register. The observed difference in the proportion of women exclusively breastfeeding for a minimum of four months corresponds to an odds ratio of 1.32. In the power calculations, an interclass correlation coefficient (ICC) of 0.001, as observed in the previous intervention study [27], was used. Reaching a statistical power of 80% with a 5% significance level is thus achievable provided data are collected from 111 mothers in each cluster. In each cluster, the sample size was extended to ensure that a minimum of 52 mothers were young or had low educational attainment. This yields a power of 80% to investigate an increase in exclusive breastfeeding at four months from 45 to 55% in this subgroup.

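### With 21 municipalities and no small-sample method named, the primary test keeps its 5% level only if the municipal ICC is about as small as the assumed 0.001

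*Protocol article*

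**What the plan says.** Under Study population: "Each of the 21 participating municipalities constitutes a cluster in the trial". Table 2 (Development and implementation) gives the size of one arm: "210 health visitors from the 11 intervention municipalities completed a preparatory 3.5-h e-learning course". That leaves 21 − 11 = 10 control municipalities.

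Under Statistical methods, clustering in the primary analysis is handled as follows: "We will account for the clustered nature of data by using random effects models for binary and continuous outcomes". Shared frailty models are named for time-to-event outcomes. Every model is run with treatment alone and again with adjustment for individual predictors and for the two randomisation variables, region and annual births (below 900, or 900 and above). The section does not name the estimator, the reference distribution, the degrees of freedom or any correction for few clusters.

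The error rate claimed is in the sample size section: "Reaching a statistical power of 80% with a 5% significance level is thus achievable provided data are collected from 111 mothers in each cluster". That calculation uses an ICC of 0.001, attributed to the previous intervention study, which the Background describes as hospital-based.

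**The concern.** Treatment varies only between municipalities, so the information about its standard error comes from 21 cluster values, less the number of cluster-level terms in the model. Two things can make a mixed-model test too liberal here. Maximum likelihood divides the between-cluster variation by 21 rather than by the residual degrees of freedom, and a normal reference ignores that this variance was itself estimated. If municipalities differ by more than an ICC of 0.001 implies, the primary p-value is too small and the confidence interval too narrow. The trial could then declare an effect more often than its stated 5% allows. This concerns the validity of the test and interval, not the sample size formula.

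**Working it through.** **1. The plan's own figure reproduces.** Inputs: 49% and 56% ("mean prevalence of breastfeeding at four months in the project regions (49%) and at national levels (56%) in 2016"), 80% power, 5% level (two-sided assumed), and for the clusters "an estimated eight clusters in each arm were used, totalling 16 clusters".
- Odds ratio = (0.56/0.44)/(0.49/0.51) = 1.325; the article gives 1.32.
- Two-proportion formula with pooled null variance: 798 per arm.
- Design effect = 1 + (111 − 1) × 0.001 = 1.11.
- 798 × 1.11 = 886 per arm; 886/8 = 110.7 per cluster, as stated (111).

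**2. Degrees of freedom.** Unadjusted: 21 − 2 = 19. With region and size: 21 − 4 = 17.

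**3. Limiting size of the uncorrected test, when between-cluster variation dominates.**
- REML variance, z cut-off 1.96: P(|t19| > 1.96) = 6.5%; P(|t17| > 1.96) = 6.7%.
- ML variance: the statistic is inflated by √(21/df), so the effective cut-off is 1.96 × √(df/21). For 19 df it is 1.864, giving 7.8%. For 17 df it is 1.763, giving 9.6%.

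**4. What an ICC means here.** Between-municipality SD = √(ICC × 0.49 × 0.51): 1.6 percentage points at 0.001, 3.5 at 0.005, 5.0 at 0.01 and 7.1 at 0.02.

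**5. Simulation under no effect.** 11 versus 10 clusters of 111, true rate 49%. The approximation uses a linear model on cluster proportions, with the variance not allowed below the binomial variance (200,000 runs per cell). The full model is a random-intercept logistic model by maximum likelihood with quadrature (1,400 to 3,000 runs per cell; Monte Carlo SE about 0.4 to 0.8 points). The allocation of municipalities to strata is assumed.

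| ICC | Unadjusted, ML z: approximation / full model | Adjusted for region and size, ML z: approximation / full model | REML z (approximation) |
|---|---|---|---|
| 0.001 | 5.2% / 4.4%, 5.9% | 5.5% / 5.8% | 4.6–4.8% |
| 0.005 | 6.9% / 7.6% | 8.0% / 9.1% | 6.0% |
| 0.01 | 7.6% / 8.8% | 9.2% / 8.7%, 8.9% | 6.4–6.6% |
| 0.02 | 7.8% / not run | 9.5% / 9.2% | 6.6–6.7% |

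Two values in a cell are two separate runs. A t-test on cluster proportions gave 4.9–5.1% at every ICC in the approximation, and 4.6–6.0% in the smaller full-model runs.

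**6. Larger clusters.** The sample is to be extended until at least 52 mothers per cluster are young or have low education. If that group is 30–40% of respondents, as expected for families overall, clusters hold 52/0.40 = 130 to 52/0.30 = 173 mothers. At 150 per cluster, the adjusted ML z-test gave 5.8% at ICC 0.001, 7.0% at 0.002 and 8.6% at 0.005.

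**7. Price of a t reference.** With 21 clusters of 111 and ICC 0.001, SE = √[1.11 × (0.56 × 0.44/1221 + 0.49 × 0.51/1110)] = 0.0218, so 0.07/SE = 3.22. Power is 89.5% with z, 86.2% with t on 19 df and 85.8% with t on 17 df.

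**The case against.** The strongest reply is that the article never says a large-sample test will be used. A random-effects model with a t reference or a Satterthwaite or Kenward–Roger type correction satisfies the quoted sentence word for word, and such detail is commonly left to an analysis plan, which is not shown. That stands: the z-test is an inference from usual software behaviour. The point is therefore a request to fix the method, not a charge that a wrong test was specified.

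A reader might infer that the planned test simply fails its 5% level with 21 clusters. The documents do not support that. The only ICC they give is 0.001, and there the level is essentially kept. The hospital origin of that value is a reason for doubt, not evidence for a larger one.

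Three further limits stand. The figures near 9% need maximum likelihood, a larger ICC and, in the main, both cluster-level covariates. The simulations omit the individual covariates, which may explain some of the variation between municipalities, so the ICCs shown are residual ones. And the frailty model was not simulated; it bears on a primary outcome only if duration is primary, as in the Abstract and Table 3 but not under Secondary outcome measures.

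The reply does not remove the dependence on the ICC. The article itself says that maternal age and education vary with municipality size and that support may vary with organisation and health visitor skill. An ICC of 0.001 allows an SD of only 1.6 points between municipalities.

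**Conclusion.** The point holds conditionally. The named model class, run in its usual form on 21 municipalities, has a type I error of about 4.4–5.9% at ICC 0.001. At ICCs of 0.005–0.02 this becomes about 7–9% unadjusted and 8–9.5% adjusted for region and size, or about 6–7% with REML. These figures assume ICCs above the documented value, a Wald z-test, equal clusters of 111 and an assumed stratum layout. No magnitude is claimed for the frailty model. This is a worthwhile, inexpensive improvement: the validity of the primary test need not rest on an ICC carried over from another setting.

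**What to change.** State that the primary test and confidence interval use a small-sample method, and name one:
- keep the random-effects model, with a restricted-likelihood type variance and a t reference on between-cluster degrees of freedom (about 17 adjusted, 19 unadjusted); or
- analyse the 21 municipality-level, covariate-adjusted proportions with strata terms and the same t reference; or
- use a permutation test within the randomisation strata.

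Under the first option the variance estimator matters. A t reference on a maximum likelihood variance still gave 7.0% at ICC 0.01 in the adjusted full model (1,400 runs), whereas the REML-type variance with t gave 3.2–5.1% across the ICCs tried, somewhat conservative at the smallest.

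Apply the same principle to the inverse-probability-weighted analysis and to the frailty model for duration.

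The cost is a sentence in the analysis plan, standard software and some nominal power: about 90% to 86% at ICC 0.001, still above the planned 80%. At ICC 0.01 the corresponding figures are 65% and 60%; there the power is lost mainly to the ICC itself.
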